### **Safety Data**

Adverse events will be coded using the Medical Dictionary for Regulatory Activities (MedDRA). For each study treatment, number of participants, percentage of participants in the treatment group and numbers of TEAEs will be tabulated by system organ class and preferred term.

The study treatment information will be listed. The actual number of dressings applied will be summarised.

For the summaries of AEs, participants who experience the same AE (in terms of the MedDRA system organ class and preferred term) more than once will only be counted once for that event in the number of participants. Categorical summaries will include the

frequency, incidences (one per participant) and percentages of events for participants and will be displayed by treatment group.

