**Risk/Benefit Assessment**

As a first-in-human trial, some unforeseen risks to participants are unavoidable; however, all existing preclinical data highlights minimal risk to human cells and wound healing. As a topical application, it is highly unlikely that any application of PAW can have systemic effects. No participant will have PAW applied until completion of an ongoing large-animal (pig) preclinical study demonstrates no ill effects.

As a novel agent applied to open wounds, it is possible that localised skin irritation may occur; the trial and care team will be aware of this as the most likely adverse reaction and tailor a care plan for cases where it eventuates in order to limit impact of irritation on the wound microenvironment and healing.

Preclinical mouse and pig models showed no signs of pain or discomfort on application of PAW, and our patients with DFU, who are predominantly neuropathic, have a decreased capacity to feel localised foot pain. If patients with incomplete loss of sensation do report any pain or discomfort from the rinse application, saline will immediately be applied to wash away PAW and the event reported as an adverse reaction.

As a Phase I study in patients without severe infection, benefits to participants are expected to be muted. We expect participants randomised to the experimental arm of this study to have reduced bacterial load and recurrent infection during study; preclinical data suggests that wound healing may also be improved for this group. Regardless, we expect participants in both groups to benefit from improved personalised care experienced by typical clinical trial participants.

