#### *Application of Treatment*

The treating clinician will identify the patient by their study ID and check that they have the appropriate ID-labelled treatment. All wound dressings should be removed, and if standard of care requires debridement of the wound, that debridement will be done prior to the application of study treatment.

A piece of sterile gauze is soaked in product, and applied to the wound for ten minutes. Other study or clinical procedures can be performed during the ten-minute period.

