#### *After the Application of Treatment*

Once dressing is applied, its application should be immediately removed if:

- in the opinion of the Investigator, a participant exhibits signs or symptoms of shock or an allergic reaction; OR
- in the opinion of the Investigator, a participant exhibits any other unacceptable AE that warrant its removal; OR
- if the participant requests its removal.

When a rinse dressing is removed, it should not be reapplied, and the time and date of removal should be recorded.

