## **9 STATISTICAL ANALYSIS**

The statistical analysis principles described below will be supplemented by a statistical analysis plan (SAP), which will be finalised before the database is locked. Any changes to the statistical plans will be described and justified in the clinical study report (CSR).

The SAP will describe procedures for accounting for missing, unused, and spurious data. This section is a summary of the planned statistical analyses of the primary and secondary endpoints.

All analyses, summaries, and listings will be performed using SAS® software (version 9.4 or higher).

The following descriptive statistics will be used as applicable to summarise the study data, unless otherwise specified:

- Continuous variables: sample size [n], mean, standard deviation [SD], median, minimum [min], and maximum [max].
- Categorical variables: frequencies and percentages.

Individual participant data will be presented in listings.

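### The planned exposure summary counts a rinse dressing removed early the same as one left on for ten minutes, and the protocol names no start time or removal reason from which the difference could be recovered

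*Protocol*

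**What the plan says.** Application of Treatment (Section 7) sets the contact time: "A piece of sterile gauze is soaked in product, and applied to the wound for ten minutes".

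After the Application of Treatment lists the grounds for immediate removal: signs of shock or allergy, "a participant exhibits any other unacceptable AE that warrant its removal", or "if the participant requests its removal". It continues: "When a rinse dressing is removed, it should not be reapplied, and the time and date of removal should be recorded".

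Safety Data (Section 9) states one exposure summary, "The actual number of dressings applied will be summarised". The sentence before it says "The study treatment information will be listed", and the opening of Section 9 adds "Individual participant data will be presented in listings". The contents of the treatment listing are not specified.

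The Risk/Benefit Assessment covers pain or discomfort during application: "saline will immediately be applied to wash away PAW and the event reported as an adverse reaction".

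Table 1 makes safety and tolerability up to six weeks the primary objective. Its outcome measure is the incidence and severity of adverse reactions.

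**The concern.** The protocol foresees that some applications will be shorter than planned, but the one exposure measure it commits to summarising cannot register this. In a first-in-human study with tolerability in the primary objective, early removal is a direct and inexpensive sign of how well the rinse is tolerated. If PAW dressings came off early more often than saline dressings, both groups could still show the same dressing count.

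The gap also lies in data capture. A removal time without a start time gives no duration. A SAP finalised before database lock can specify a table, but it cannot supply a field that was never collected.

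**Working it through.** The protocol gives no figure for contact time or total exposure, so there is nothing to reproduce. The check traces each kind of early removal through the planned outputs, then illustrates what the count can miss.

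**Where each early removal would show**

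- *Shock or allergic signs, or another unacceptable adverse event.* These are adverse events under Section 5 and enter the tables described in Safety Data. The dressing counts as one applied.
- *Pain or discomfort.* Reported as an adverse reaction under the Risk/Benefit Assessment, so also tabulated. The dressing counts as one applied.
- *Participant request with no reported symptom.* Need not be an adverse event. The dressing counts as one applied. At most a removal time appears in a listing.
- *Intolerance that leads to discontinuation.* Withdrawal of Participants from Study names it as a possible reason, at the Principal Investigator's discretion. Demographics and Baseline Data summarises discontinuations by reason.

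In none of the four is the lost contact time summarised by group.

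**Fields named for an application**

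- Time and date of removal: named.
- Start time: not named.
- Duration of contact: not named.
- Reason for removal: not named for the application. Where the removal follows an adverse event, the event record includes actions taken, so a reason may be recoverable there.

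Duration is removal time minus start time, so it cannot be computed from the named fields.

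**Illustration (all removal times are assumed)**

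Let *k* be the number of applications and *m* the minutes before removal. Planned contact is 10*k* minutes. If every application is removed at *m* minutes, contact is *km*, a share of *km*/10*k* = *m*/10. The dressing count is *k* of *k*, or 100%, whatever *m* is.

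With *k* = 6 (study treatment marked at Visits 1 to 6 in the schedule table), planned contact is 60 minutes:

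- *m* = 1: 6 of 60 minutes, 10%
- *m* = 2: 12 of 60 minutes, 20%
- *m* = 5: 30 of 60 minutes, 50%
- *m* = 9: 54 of 60 minutes, 90%

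If the 12 visits over six weeks given in Overall Study Design were all treatment visits, planned contact would be 120 minutes. The shares would be unchanged, because *k* cancels.

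A milder case is one of six applications removed at 2 minutes: (5 × 10 + 2)/60 = 52/60 = 87% of planned contact, again shown as six dressings.

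For a group of ten in which *j* participants have every dressing removed at 2 minutes, mean contact is [(10 − *j*) × 60 + *j* × 12]/10:

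- *j* = 1: 55.2 minutes
- *j* = 2: 50.4 minutes
- *j* = 3: 45.6 minutes, or 456 of 600 group minutes, 76%
- *j* = 5: 36.0 minutes

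The mean dressing count is 6.0 in every case.

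**The case against.** The strongest reply is that Section 9 describes itself as a summary to be supplemented by a SAP. Exposure tables are often set there, and case report form fields in the data-capture specification. Neither document is shown, and Safety Data does not say that the count will be the only exposure summary. Treatment information will also be listed. With 20 participants and six applications each, that is about 120 records, few enough to read one by one.

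This stands in part. A SAP could add the table, and the REDCap forms may already hold a start time. But the protocol itself names the removal time and stops there, and the SAP may be finalised too late to restore a missing field.

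Three stronger readings are tempting, and the documents do not support them:

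- *A participant who never tolerates ten minutes is classed as fully treated.* No section defines full treatment, compliance or evaluability by dressing count.
- *Reaction rates are diluted by overstated exposure.* Adverse events are reported as numbers and percentages of participants in the group, each counted once per event. Neither dressings nor minutes form the denominator.
- *Intolerance is hidden.* Removals for pain, allergy or another adverse event reach the adverse event tables, and discontinuations are summarised by reason.

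Repeated very short applications are also an extreme case. The section on postponing or stopping treatment says not to apply it where the investigator sees a risk that it will not be tolerated, so such a participant may never reach the full count.

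**Conclusion.** The point holds in a limited form. The stated exposure summary does not distinguish a shortened application from a completed one, and contact time cannot be derived from the fields the protocol names. What is lost is a comparison between groups of how often treatment was cut short, including removals on request without a symptom.

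The size in practice is unknown, because the protocol gives no expected frequency of early removal. The illustration shows only that a full dressing count is compatible with 10% to 90% of planned contact at the assumed removal times. The conclusion assumes that the data-capture forms follow the protocol text. If they already record start time and reason, only the summary needs changing. Priority is minor to moderate.

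Planned exposure itself cannot be stated until the six treatment visits in the schedule table and the 12 visits over six weeks in Overall Study Design are reconciled.

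**What to change.** In Section 7, require the start time, stop time and reason for removal to be recorded for every application, with participant request as one of the reasons.

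In Safety Data, replace the single count with a summary by treatment group:

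- applications started;
- applications completed to the planned ten minutes;
- applications removed early, by reason;
- participants with at least one early removal.

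Present this as a tolerability summary beside the adverse reactions. Contact minutes can then be derived and listed or summarised.

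Reconcile the planned number of applications between the schedule table and Overall Study Design.

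The cost is a few REDCap fields per treatment visit, the associated data entry and one extra table. No visits or procedures are added, and clinical management does not change. The fields should be in place before the first participant is treated.

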### **Clinical Laboratory Evaluations**

Laboratory data (haematology, clinical chemistry, HbA1c) will be summarised for each treatment group using descriptive statistics at each protocol scheduled visit for actual values and changes from baseline.

Abnormal laboratory values will be flagged and will be identified in the listings. Microscopy data, if available, will be listed.

The incidence of treatment-emergent abnormal laboratory findings will be summarised using frequency counts and percentages for each treatment group and listed separately.

### **Vital Signs Analysis**

Vital signs (including height, weight and BMI) will be summarised for each treatment group using descriptive statistics at each protocol scheduled time point for actual values and change from baseline.

### **Other Safety Measures**

Physical Examination findings will be listed only.

## **10 STUDY MANAGEMENT**

### **Quality Control and Quality Assurance**

All study tasks will be performed in accordance with applicable regulations, ICH Good Clinical Practice (GCP), and study site Standard Operating Procedures (SOPs).

During the study, CALHN Research Office staff may regularly visit the site to monitor and confirm protocol, regulatory and ethical adherence, confirm data accuracy and provide information and support as needed.

The PI agrees to allow designated CALHN personnel direct access to all relevant documents, including electronic medical records, and to allocate his time and the time of his staff to the CRA to discuss findings and any relevant issues.

### **Data Protection**

The PICF will explain that study data will be stored in a computer database, maintaining confidentiality in accordance with national data legislation. In this database participants will be identified by participant ID number only. The PICF will also explain that for data verification purposes, authorised representatives of the Sponsor, regulatory authorities, IECs or sites may require direct access to parts of the hospital or site records relevant to the study, including personal participant information.

### **Archiving**

The Investigator is responsible for the archiving of the study records for their site. Study records include the participant files as well as the source data, the Investigator Site File,

pharmacy records, and other study documents. Study records must be archived for at least 15 years. After 15 years, secure destruction of data (shredding of paper copies, secure deletion of REDCap resources) will be directed by [name] or delegate.

If the Investigator leaves the investigational site for any reason, the responsibility for all study related records must be transferred to another person at site.

